### Cost-effectiveness analysis

The incremental cost-effectiveness ratio (ICER) will be calculated considering the incidence of severe degrees of OM as the measure of effectiveness for the PBMT and control groups. We will also measure the effectiveness based on patient-reported outcomes (including QoL measures). A decision tree-type diagram will be created to represent all clinically relevant events.

The ICER will be calculated to determine the cost-effectiveness of PBMT. The ICER will be calculated by dividing the cost difference (Cost2 – Cost1) by the difference between the frequency of severe OM in both groups. The ICER will represent the incremental cost to avoid one case of severe OM using PBMT.

Additionally, another ICER will be calculated by dividing the cost difference (Cost2 – Cost1) by the difference between the QoL in both groups. The ICER represents the incremental cost to avoid the loss of 1 point on the QoL measure, assessed using the difference between the last evaluation (30th RT) and the baseline (0 RT). Two different ICERs will be calculated considering the scores of each instrument (OHIP-14 and PROMS). The following formula summarizes the ICER analysis.$$ \mathrm{ICER}=\left(\mathrm{Cost}2-\mathrm{Cost}1\right)/\left(\mathrm{QoL}2-\mathrm{QoL}1\right) $$

Univariate sensitivity analysis will be performed to assess the uncertainty in the parameters associated with PBMT.

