Antunes et al. [29] conducted a cost-effectiveness study regarding the use of PBMT in the treatment of OM, taking into consideration the public health system perspective and the prevention of severe OM as the effectiveness measure. The authors concluded that the patients treated with PBMT presented an incremental cost of US$1689.00, when compared with the patients not exposed to PBMT; the incremental cost-effectiveness ratio was US$4961.37 per severe case of OM prevented. To our knowledge, there has not been a study that has evaluated the cost-effectiveness of PBMT for the control and treatment of OM based on patient-reported outcomes. This type of study may allow a comparison between the different technologies and drugs used for the treatment of OM.

Thus, the aim of this study is to assess the cost-effectiveness and molecular effects of PBMT in the treatment and prevention of severe OM. The hypothesis is that PBMT is more costly but more effective than conventional treatment of OM and that PBMT modulates the inflammatory and oxidative stress proteins. This study will contribute to a better understanding of the PBMT mechanism and may allow the laser technology to be consolidated and used in public health systems, providing a better QoL for patients undergoing HNC treatment.

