### Randomization and blinding/masking

Participants will be randomly assigned into two groups: group 1 (PBMT, five times per week) and group 2 (control). A computer-based random number generator (www.randomizer.org) will be used to assign the participants to the study groups. Simple randomization will be performed with an allocation ratio of 1:1. The sequence will be generated by an independent collaborator. The letters A and B will be used to determine the group: A = intervention and B = control. The sequence will be concealed in consecutively numbered opaque envelopes. Each envelope will be opened at the time of the first RT session. The participants will be blinded to the allocation group. In the control group, a sham laser will be used; the participants will hear the characteristic sound of the equipment but no irradiation will be performed. The researcher responsible for assessing the OM will also be blind regarding the study group and will not have contact with the participants since the assessment will be carried out using the photographs of the participants.

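### The printed quality-of-life ICER has the wrong sign for OHIP-14 and PROMS if higher scores are worse, and the one uncertainty analysis named cannot reflect joint sampling error in cost and effect

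*Protocol article*

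**What the plan says.** All the ICER definitions are in the protocol article, Cost-effectiveness analysis.

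- **Quality of life.** The printed formula is ICER = (Cost2 – Cost1)/(QoL2 – QoL1). It is used twice: "Two different ICERs will be calculated considering the scores of each instrument (OHIP-14 and PROMS"). The quality-of-life quantity is a change, "assessed using the difference between the last evaluation (30th RT) and the baseline (0 RT"). The result is interpreted as follows: "The ICER represents the incremental cost to avoid the loss of 1 point on the QoL measure".
- **Severe mucositis.** The ratio is obtained by "dividing the cost difference (Cost2 – Cost1) by the difference between the frequency of severe OM in both groups". No order of subtraction is given for the denominator. The interpretation is "The ICER will represent the incremental cost to avoid one case of severe OM using PBMT".
- **Indices.** Arms 1 and 2 are not defined in that section. Randomization and blinding/masking numbers them "group 1 (PBMT, five times per week) and group 2 (control").
- **Expected direction.** Background states: "The hypothesis is that PBMT is more costly but more effective than conventional treatment of OM".
- **Instruments.** Quality of life (under Outcomes) describes OHIP-14 as a sum over subscales of limitation, pain, discomfort, disability and handicap, and PROMS as the sum of ten visual-analogue items on mucositis symptoms. It does not say which end of either score is favourable.
- **Uncertainty.** One analysis is named: "Univariate sensitivity analysis will be performed to assess the uncertainty in the parameters associated with PBMT". Statistical analysis of data contains nothing on costs or ICERs.

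**The concern.** An ICER carries a plain meaning only if cost and benefit are both signed so that a positive denominator is a gain. On a score where more points mean more impairment, losing a point is an improvement, so the interpretation given for the quality-of-life ICER describes avoiding a benefit. The formula has the same fault: a better result for PBMT makes the denominator run against the numerator.

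This matters because a negative ICER is commonly read as dominance (cheaper and better). The result the trial expects, dearer and better, would come out negative, and true dominance would come out positive. The article presents patient-reported effectiveness as its new contribution and addresses the result to public policy-makers, so these are the ratios most likely to be quoted.

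A second, smaller issue is precision. With about 25 patients per arm, both the effect difference and the cost difference are estimated with appreciable error. Varying PBMT parameters one at a time does not show their combined effect, and as worded it leaves out the unit costs of severe mucositis.

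**Working it through.** **1. Planning figure reproduced.** Inputs from Participants: severe mucositis 60% (control) and 21% (PBMT), 5% significance (taken as two-sided), 80% power, 1:1. With pooled variance and mean proportion 0.405, n per arm = (1.960 + 0.842)² × 2 × 0.405 × 0.595 / 0.39² = 24.87, so 25 per arm and 50 in total, as stated. The sample size is not in question; it supplies the n for step 4.

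**2. Sign of the quality-of-life ratio.** Let ΔC be PBMT cost minus control cost, and let ΔW be mean worsening (30th session minus baseline, higher is worse) under PBMT minus that under control.

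- If arm 2 is PBMT, the formula gives ΔC/ΔW.
- If arm 2 is control, as the group numbering suggests, it gives (–ΔC)/(–ΔW) = ΔC/ΔW.

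Relabelling therefore changes nothing. The four cases are:

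| PBMT is | ΔC | ΔW | Printed formula | Per point of worsening avoided, ΔC/(–ΔW) |
|---|---|---|---|---|
| dearer, better (hypothesis) | + | – | negative | positive |
| cheaper, better | – | – | positive | negative |
| dearer, worse | + | + | positive | negative |
| cheaper, worse | – | + | negative | positive |

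In every row the printed formula has the opposite sign to the cost per point avoided. A numerical illustration takes the incremental cost of US$1689 from the earlier cost-effectiveness study cited in Background and *assumes* mean worsening of 10 points (PBMT) and 20 points (control). The printed formula gives 1689/(10 – 20) = –168.9 with arm 2 as PBMT, and –1689/(20 – 10) = –168.9 with arm 2 as control. Cost per point of worsening avoided is 1689/(20 – 10) = +168.9.

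**3. Severe-mucositis ratio.** With the planning rates and the same US$1689, subtracting in the same order as the costs gives 1689/(0.21 – 0.60) = –4331. Subtracting as cases avoided gives 1689/(0.60 – 0.21) = +4331. The article does not say which order applies, and its stated interpretation matches the second. The cited study's positive ICER of US$4961.37 also implies a difference expressed as cases prevented: 1689/4961.37 = 0.340.

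**4. Sampling error in the effect alone.** Standard error of the risk difference at 25 per arm = √(0.60 × 0.40/25 + 0.21 × 0.79/25) = 0.1274. The 95% CI is 0.39 ± 1.96 × 0.1274, or 0.140 to 0.640. With any fixed cost difference the ICER is proportional to 1/(risk difference), so it runs from 0.39/0.640 = 0.61 to 0.39/0.140 = 2.78 times its central value. The ratio of the ends is 0.640/0.140, about 4.6. At US$1689 this would be about US$2,640 to US$12,042 around US$4,331.

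**5. Adding sampling error in cost.** The article gives no cost standard deviation, so a range was assumed. Simulation used 25 per arm, a normal cost difference centred on US$1689 and independent of the effect, and dropped the roughly 0.25% of replicates with no effect or a negative one.

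| Assumed per-patient cost SD (US$) | Approximate 95% range of ICER (US$) |
|---|---|
| 1000 | 2,300 to 12,500 |
| 2000 | 1,360 to 13,300 |
| 4000 | –1,410 to 16,000 |

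These figures show scale only. They combine another study's cost with this trial's planning rates and are not forecasts of the trial's ICER.

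**The case against.** **Direction is inferred.** The article states no scoring direction for either instrument. That is true, and the sign argument depends on it. But sums of limitation, pain, disability and symptom items point strongly one way, and nothing in the text mentions reverse scoring.

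**The wording can be read charitably.** A lost point of quality of life may simply mean one point of deterioration, which is the quantity wanted. The sign would also come right if the change were taken as baseline minus 30th session. The text names the last evaluation first and the baseline second, which most naturally means the reverse. An analyst who follows the printed formula literally gets the wrong sign.

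**Reporting would prevent misreading.** If incremental cost and effect are shown beside the ratio, and the expected direction is recalled, few readers would be misled. This limits the harm. It does not make the formula agree with its interpretation.

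**Severe mucositis.** A reader might infer that this ICER has the same error. The text does not support that: it fixes no subtraction order, and its stated interpretation is right. This objection stands.

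**Uncertainty.** A reader might also infer that no interval is planned for any ICER. A condensed article's silence cannot establish that, and a fuller document may provide one. The parameters associated with PBMT could, in the planned decision tree, include the probability of severe mucositis under PBMT, so it is not shown that the effect is left fixed. Both objections stand. What remains is that one-at-a-time variation, however widely its parameters are read, cannot represent joint sampling error or the correlation of cost with effect.

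**Conclusion.** The concern holds for the quality-of-life ICERs. The printed formula and its interpretation contradict the evident direction of OHIP-14 and PROMS: the hypothesised result would be negative under either arm numbering, and a cheaper and better PBMT would be positive. The absolute size of the ratio is unaffected; its sign and meaning are. This rests on higher scores being worse (inferred from content) and on change being taken as 30th session minus baseline.

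The severe-mucositis ICER is ambiguous, not wrong. On uncertainty, the supportable statement is limited: the one analysis named would not convey joint sampling error and, as worded, does not cover the costs of severe mucositis. At the planning rates, effect sampling error alone spans about a 4.6-fold range of ICER at a fixed cost difference. The documents do not support the stronger claims that every ICER has the wrong sign or that no interval will be produced.

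**What to change.** In Cost-effectiveness analysis:

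1. Replace the undefined indices. Cost difference = PBMT minus control.
2. Define effect as control minus PBMT, for the proportion with severe mucositis and for mean worsening from baseline (30th session minus baseline) in OHIP-14 and in PROMS.
3. State the scoring direction of each instrument.
4. Label the ratios *cost per severe case avoided* and *cost per point of worsening avoided*. With each, report incremental cost, incremental effect and the quadrant of the cost-effectiveness plane.
5. Add a non-parametric bootstrap that resamples patient-level cost-effect pairs within arm, shown on the cost-effectiveness plane or as a net-benefit interval. If a fuller document already specifies this, refer to it.
6. Include the unit costs of severe mucositis (hospitalization, opioids, parenteral nutrition) in the univariate sensitivity analysis.

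The cost is a few sentences and a short script, with no additional patients or outcome data. The drawback is that the reported precision will look less favourable.

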**Methods/design:**

This randomized, double-blind clinical trial will include 50 HNC patients undergoing radiotherapy or chemoradiotherapy. The participants will be randomized into two groups: intervention group (photobiomodulation) and control group (preventive oral care protocol). OM (clinical assessment), saliva (assessment of collected samples) and quality of life (Oral Health Impact Profile-14 and Patient-Reported Oral Mucositis Symptoms questionnaires) will be assessed at the 1st, 7th, 14th, 21st and 30th radiotherapy sessions. Oxidative stress and inflammatory cytokine levels will be measured in the saliva samples of all participants. The costs are identified, measured and evaluated considering the radiotherapy time interval. The incremental cost-effectiveness ratio will be estimated. The study will be conducted according to the Brazilian public health system perspective.

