### Participants

The participants will be HNC patients of the Brazilian public health system—Brazilian Unified Health System (Sistema Único de Saúde (SUS))—who will be treated with RT, with or without CT, in Araujo Jorge Hospital, Goiânia, Goiás, Brazil. To estimate the study sample size, we used the OpenEpi online calculator (http://www.openepi.com). The 95% significance level (1 – α error type I), a study power of 80% (1 – β error type II) and a 1.0 ratio of unexposed/exposed were set as estimator parameters. Finally, we considered a prevalence of severe OM of 60% for the control group and 21% for the PBMT group (OR = 0.18) [18]. The calculated minimum sample size was 50 participants (25 per group) and an additional 10% was considered to compensate for possible loss to follow-up.

Individuals older than 18 years of age of both sexes will be included in the study, edentulous or not, with neoplastic lesions in the head and neck site (oral cavity, oropharynx, nasopharynx and advanced stage laryngeal tumors; T3 N1 or T3 N2 and T4 with any N status). All participants will be subjected to RT (with or without CT), with a minimum dose of 50 Gy, 2 Gy/day and five times per week, in the conventional scheme of RT. All patients will be treated with the Elekta Compact (Elekta AB, Stockholm, Sweden), a linear accelerator that generates photon radiation with fixed energy of 6 MV. Participants will be excluded if they present with an infection or salivary gland tumors, Sjögren’s syndrome, are submitted to palliative treatment or were previously treated with RT and/or CT in the head and neck area. Individuals diagnosed with lymphoma, melanoma or skin cancer will also be excluded.

In this hospital setting, every HNC patient who will be submitted to RT must be evaluated by the Dental Care Service to obtain authorization before starting the HNC treatment. On this occasion, the individuals will be invited to participate in the study. After acceptance, the principle researcher will obtain a signed written informed consent form from the participants. Participants will be excluded from the trial in cases of death, withdrawal or absence from five or more laser therapy sessions.

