### Study groups

#### Group 1: photobiomodulation therapy

The participants in this group will be submitted to laser therapy five times a week, during the RT. The PBMT protocol will begin in the first RT session, be conducted before each RT session and continue until the end of the treatment. Since the RT sessions will be scheduled in a specific hour, it will be possible to control participant appointments. If severe OM develops at the end of the RT, the patient will receive additional sessions.

The Twin Flex Evolution Laser (MMOptics, São Paulo, Brazil) will be used at a wavelength of 660 nm (red laser), 25 mW of power, in continuous mode, with punctual and perpendicular application in contact with the mucosa. The transferred energy will be 6.2 J/cm^2^ for 10 s on a spot area of 0.04 cm^2^, and thus energy of approximately 0.25 J will be deposited at each point. Before each session, the tip of the laser will be disinfected with a solution of 70% alcohol and wrapped in a plastic film. The laser beam will not be irradiated in a malignant lesion smaller than 1 cm if observed, or near a surgical site.

Specific anatomical regions be considered for the PBMT: right and left buccal mucosa (10 points on each side), upper and lower labial mucosa (four points on each lip), hard palate (three points), lateral surface of the tongue (10 points on each side), soft palate (three points), dorsal tongue (three points), floor of the mouth (two points) and labial commissure (one point on each side). This protocol is based on a previous study by Oton-Leite et al. [30].

The participants will also be submitted to a dental care protocol that consists of elimination of the infection focus, a fluoride rinse, a chlorhexidine 0.12% rinse three times a day diluted in water in a 1:1 proportion, recommendation to drink at least 1.5 L of water per day and the maintenance of good oral hygiene. If the presence of OM is observed, an oral ointment with hydrocortisone 5 mg, neomycin 5 mg, troxerutin 20 mg, ascorbic acid 0.5 mg and benzocaine 2 mg will be prescribed (Gingilone; Farmasa, São Paulo, Brazil).

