#### Quality of life

The translated, adapted and validated Brazilian version [33] of the Oral Health Impact Profile, in its simplified form (OHIP-14) [34], will be used to assess the oral health-related quality of the participants. This questionnaire contains 14 questions, divided into seven subscales: functional limitation, physical pain, physiological discomfort, physical disability, physiological disability, social disability and handicap. The questions will be answered on a 5-point Likert scale, the responses will be summarized and the final score will be calculated.

The translated version of the Patient-Reported Oral Mucositis Symptoms (PROMS) scale will also be used to assess the OM effects reported by the patient [35]. This scale was originally used to assess OM due to CT; however, its use in patients undergoing RT is also feasible [36, 37]. The scale contains 10 questions, which are answered on a 10-cm uninterrupted visual analog scale. The participant will be asked to indicate the score for each item. The sum of the 10 items will be used as the PROMS score.

These instruments will be applied during the first appointment and after the 7th, 14th, 21st and 30th RT sessions based on previous studies [23, 38] that also evaluated the QoL weekly. As reported earlier, the OM evaluation will occur at the same time points. The questionnaires will be applied before the PBMT session and if the participant is not able to answer, a calibrated healthcare professional will provide help.

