#### Estimation of costs

##### PBMT costs

Cost estimation will include the direct costs of resources associated with the treatment of OM during RT. All fixed and variable costs will be identified, measured and valuated for each cost item. The variable costs will include consumable items (70% ethanol, gauzes, procedure gloves, etc.). The fixed costs will include the income of the professionals and costs associated with the laser equipment. For the equivalent annual cost (EAC) of durable goods, a discount rate of 5% and a usage life of 5 years will be considered for calculation, using the following formula:$$ \mathrm{EAC}=\left(n\times x\right)/\left(1-1/\left[{\left(1+n\right)}^t\right]\right) $$

where EAC = annual cost equivalent, *t* = useful life, *x* = purchase price and *n* = discount index.

The average cost per PBMT session will be calculated as the sum of the variable and fixed costs. The cost of staff will consider the value of the work hours proportional to the time spent in each session: (Monthly wage / monthly working time) × time spent.

The data on costs of consumables will be obtained from the administrative department of the hospital and the cost of the laser equipment will be based on mean market prices. Costs will be estimated in Brazilian currency (Brazilian Real (BRL)) and later converted to international dollars using the purchasing power parity exchange rate.

The costs of RT and CT and those related to the routine preventive oral health protocol will not be considered since they are similar for both groups. Besides that, the social costs related to wider societal costs (e.g., loss of productivity resulting from treatment, family costs, etc.) will not be considered. Similarly, other capital costs or those associated with implementation of the dental care service will not be included.

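### Both quality-of-life ICERs rest on a raw session-30-minus-baseline change, so QoL differences at sessions 7, 14 and 21 do not count although costs accumulate over radiotherapy

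*Protocol article*

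**What the plan says.** The Cost-effectiveness analysis section divides the cost difference by the QoL difference between groups, with QoL "assessed using the difference between the last evaluation" (session 30) and the baseline (session 0). One such ratio is planned for OHIP-14 and one for PROMS. The section describes no time-averaged or baseline-adjusted QoL effect.

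The Quality of life section sets five assessments: "These instruments will be applied during the first appointment and after the 7th, 14th, 21st and 30th RT sessions".

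On costs, the Abstract states: "The costs are identified, measured and evaluated considering the radiotherapy time interval". The section on PBMT costs agrees: "Cost estimation will include the direct costs of resources associated with the treatment of OM during RT". The laser treatment that generates those costs starts at the first session and is to "be conducted before each RT session and continue until the end of the treatment".

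The Discussion presents the patient-reported ICER as the new element of the study, and it closes by naming better QoL during treatment as the benefit sought.

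**The concern.** The numerator of each QoL ICER adds up cost over the course. The denominator is the difference between arms at a single late visit. Relief from mucositis at sessions 7 to 21 earns no credit, and a contrast that appears only at session 30 is set in full against whole-course costs. Either way, the ratio does not measure QoL gained over the period in which the money was spent.

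A second, smaller matter is that a raw change score uses the baseline with a fixed coefficient of 1. Regression on baseline lets the data choose the coefficient. In large samples it is never less precise.

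At stake is the figure the trial offers to public policy-makers. The planned univariate sensitivity analysis varies parameters associated with PBMT, so as described it would not show how far the ICER depends on which QoL summary was chosen.

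**Working it through.** **Inputs.** The documents give the visit schedule and 25 participants per group. The sample-size figure is not in dispute: 60% against 21% severe mucositis, with two-sided 5% and 80% power, gives 24 per arm, or 25 if the PBMT rate is derived from the odds ratio of 0.18. They give no QoL SD, no correlation between visits and no QoL figure for the ICERs. The trajectories, SDs and correlations below are therefore assumptions. Baseline is placed at session 1.

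**Step 1: weight of the omitted visits.** A trapezoid average over sessions 1, 7, 14, 21 and 30 spans 29 sessions, in intervals of 6, 7, 7 and 9. Each visit's weight is half the adjoining intervals divided by 29.

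| Session | 1 | 7 | 14 | 21 | 30 |
|---|---|---|---|---|---|
| Weight | 3/29 = 0.10 | 6.5/29 = 0.22 | 7/29 = 0.24 | 8/29 = 0.28 | 4.5/29 = 0.16 |

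Sessions 7, 14 and 21 together carry 21.5/29 = 74%.

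**Step 2: effect on the ICER.** With the same cost difference, the session-30 ICER divided by the time-averaged ICER equals the time-averaged effect divided by the session-30 effect.

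| Assumed arm differences | Time-averaged effect | Session-30 effect | ICER ratio |
|---|---|---|---|
| 0/2/6/6/2 | (6 + 28 + 42 + 36)/29 = 3.86 | 2 | 1.93 |
| 0/4/4/4/4 | (12 + 28 + 28 + 36)/29 = 3.59 | 4 | 0.90 |
| 0/0/1/3/6 | (0 + 3.5 + 14 + 40.5)/29 = 2.00 | 6 | 0.33 |

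**Step 3: precision, with the target held at session 30.** Take SD 1 at session 30, baseline SD k and correlation r. The variance of the change score is 1 + k² − 2rk. The variance after baseline adjustment is 1 − r². The SE of the arm difference is √(2 × variance/25).

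| r (k = 1) | Change variance | Adjusted variance | SE, change | SE, adjusted | SE reduction |
|---|---|---|---|---|---|
| 0.3 | 1.40 | 0.91 | 0.335 | 0.270 | 19% |
| 0.5 | 1.00 | 0.75 | 0.283 | 0.245 | 13% |
| 0.7 | 0.60 | 0.51 | 0.219 | 0.202 | 8% |

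With k = 0.5 the variances are 0.95 against 0.91 at r = 0.3, 0.75 against 0.75 at r = 0.5, and 0.55 against 0.51 at r = 0.7. The SE falls by about 2%, 0% and 4%.

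**Step 4: does averaging steady the ratio?** What matters for a ratio is SE divided by effect. The model is the same, with equal correlation between all visits, SD 1 throughout and differences in SD units. Only the comparison between the two columns matters, not the absolute level.

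| Assumed differences | r | Session-30 change | Baseline-adjusted time average |
|---|---|---|---|
| 0/0/1/3/6 | 0.3 / 0.5 / 0.7 | 0.056 / 0.047 / 0.037 | 0.079 / 0.078 / 0.068 |
| 0/1/2/3/4 | 0.3 / 0.5 / 0.7 | 0.084 / 0.071 / 0.055 | 0.074 / 0.073 / 0.063 |
| 0/4/4/4/4 | 0.3 / 0.5 / 0.7 | 0.084 / 0.071 / 0.055 | 0.044 / 0.044 / 0.038 |
| 0/2/6/6/2 | 0.3 / 0.5 / 0.7 | 0.167 / 0.141 / 0.110 | 0.041 / 0.040 / 0.035 |

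Averaging clearly steadies the ratio when the effect is flat or peaks mid-course. It does not when the effect grows late.

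**The case against.** The strongest reply is that cost per point of QoL preserved at the end of the schedule is a coherent quantity, stated in advance with its interpretation. A time average is then a different estimand and not the correction of an error. The Background says that mucositis severity depends on the number of sessions, so a late-growing difference is plausible, and step 4 shows that the planned measure is then the steadier one. This stands, and it is why precision is not the main argument. It does not remove the mismatch between a whole-course numerator and a single-visit denominator.

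Four stronger readings are tempting, and the documents do not support them.

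- A reader might infer that using all visits cuts the SE by 31% to 48%. That comes from setting the change score against an unweighted mean of the four post-baseline visits (SE 0.18, 0.17 and 0.15 against 0.33, 0.28 and 0.22). The two estimate different effects, and the mean is not the trapezoid average either.
- A reader might infer that the intermediate visits are thrown away. They are left out of the QoL ICERs only. The within-group Friedman test in the Statistical analysis section may still use them, though it yields no between-arm effect for an ICER.
- A reader might infer that the choice works against PBMT, or makes the ICER explode. Step 2 shows movement in both directions, and any ICER diverges as its effect nears zero.
- A reader might infer that a time average fully matches the cost window. QoL collection stops at session 30 while PBMT runs to the end of treatment, so for longer courses the match is only partial.

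**Conclusion.** The point holds in a limited form. The protocol explicitly fixes both QoL ICERs on a raw session-30 change. Visits that carry 74% of a time-weighted mean therefore do not enter, although costs cover radiotherapy and the declared interest is QoL during treatment. Under the assumed trajectories the ICER moves by a factor between 0.33 and 1.93 with no change in cost. The direction cannot be known in advance, which is the reason to settle the measure before analysis.

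The precision gain is secondary. At a fixed session-30 target, baseline adjustment saves about 8% to 19% of the SE if the SDs are equal and correlations lie between 0.3 and 0.7. It saves little or nothing if baseline scores vary about half as much as session-30 scores. The case for time-averaging rests on matching the cost window.

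**What to change.** For OHIP-14 and PROMS, define the QoL effect in the ICER as the baseline-adjusted between-arm difference (ANCOVA or a repeated-measures model) in the time-averaged score over the assessments from baseline to session 30. Report the session-30 ICER as well, using a baseline-adjusted difference in place of the raw change. State that for courses longer than 30 sessions the QoL window ends before the cost window.

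The Participants section admits courses "with a minimum dose of 50 Gy, 2 Gy/day and five times per week". At the minimum, 50/2 = 25 sessions, so such a course has no on-treatment session-30 score. The proposed average does not cure this, and the passages on course length and on the session-30 assessment need to be reconciled.

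The cost is a change of wording and minor analysis work, with no new visits or participants. The downside is a change of unit: the main QoL ICER reads per average point over radiotherapy instead of per point at session 30. Keeping the session-30 ICER alongside it preserves the planned interpretation.
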